## Abstract

**Background:**

Prior studies addressing the impacts of regular physical activity or sedentary habits on the immune system have been conducted in adults and laboratory settings. Thus, it is practically unknown how a healthy active lifestyle could affect low-grade inflammation processes, infections or allergies in young persons. The AFINOS Study was designed to determine the relationship between the regular physical activity levels of adolescents and overweight, infection, and allergies along with the presence of metabolic and immunological biomarkers of a deteriorated health status. A further objective of the AFINOS Study is to assess the health status and lifestyle habits of an adolescent population in an effort to identify any protective factors that could be used as preventive measures, since many chronic diseases and their associated co-morbidities often persist from adolescence into adulthood.

**Methods/Design:**

This study was conducted as three separate sub-studies in three different populations as follows: (a) Study 1 was performed on a population sample of adolescents; (b) Study 2 on the adolescents' parents; and (c) Study 3 on a subset of the adolescents from Study 1. Study 1 assessed health and lifestyle indicators through a questionnaire administered to a representative sample of adolescents from the Madrid Region (n = 2400) aged 13 to 16 years. In Study 2, the parents of the teenagers participating in Study 1 were required to fill out a questionnaire. Finally in Study 3, body composition, physical activity, health-related physical fitness, and blood measurements were determined in a subset (n = 200) of the individuals included in Study 1.

**Discussion:**

This paper describes the rationale, design, and methodologies used in the AFINOS Study. This multidisciplinary, multicenter study seeks to evaluate several aspects of existing relationships between routine physical activity/sedentary behaviour and several health status markers, specifically those related to the immune system. The results of this cross-sectional study will serve for comparisons with the available data obtained in laboratory settings and in adults. In addition, knowledge regarding the health status and lifestyle habits of Spanish adolescents and their parents will be useful for designing preventive measures.

## Background

A link between physical activity and health has been inferred from the epidemiological evidence obtained over the past few decades. However, although this link has been clearly established in adults [1,2], knowledge about the impacts of physical activity on the health of children and adolescents is still lacking. To examine this issue, the US Centers for Disease Control conducted a review of the scientific literature that was published in 2005 [3]. This review concluded that moderate to vigorous physical activity in children and adolescents confers protection against a considerable number of health disorders, such as obesity or cardiovascular and metabolic diseases (high blood pressure, an altered blood lipid profile, metabolic syndrome, diabetes or inflammation). A further conclusion was that physical activity produces health benefits related to overall physical fitness (aerobic fitness, strength and muscular endurance) and bone density along with improved symptoms of asthma and several aspects of mental health (anxiety, depression, self-concept, academic performance, memory and classroom behaviour). On the other hand, the report highlights that there is insufficient evidence to clarify the potential effects of physical activity on the immune system of children and adolescents.

The relationship between physical activity and several health indicators in children and adolescents needs addressing further if we are to improve current knowledge of the effects physical activity may have on the health of individuals of this age. To date, the extent to which an active or inactive lifestyle could alter the immune system of adolescents remains unclear. Most studies that have assessed the relationship between physical activity and immunological markers have been carried out in laboratory settings, in which only information on the acute effects of isolated exercise sessions can be obtained. Moreover, most of these studies have been performed in adults [4] and very few investigations have examined the issue in children or adolescents [5]. According to the literature, light or moderate physical activity may enhance the immune system while intense physical activity could have the opposite effect of depleting the system [5]. There is therefore a need to assess under free-living conditions the effects on the immune system of different levels of physical activity. This type of investigation will provide insight into the long-term chronic effects of physical exercise on the health of adolescents, as an age group of particular interest, since any benefits or negative repercussions are likely to continue into adulthood.

Obesity is a health problem that has been declared by the WHO as a global epidemic, whose prevalence has been growing rapidly in many areas of the world [6]. Especially worrying, is the rapidly increasing incidence of overweight or obesity observed in the young people of many countries [7]. This trend indicates there will be a rise in the prevalence of obesity in adult populations of the near future accompanied by a wider spectrum of obesity-related diseases at increasingly earlier ages. Due to the high economic and social costs associated with obesity and its co-morbidities [8,9], obesity prevention is a priority objective that requires further knowledge of the factors that are converting the present generation of children and adolescents into the most obese in history. In Spain, the situation is similar to that of any other developed country, and we are seeing a rapidly rising trend in the number of children and adolescents of both sexes who are overweight or obese [10,11]. To combat this outbreak, the Spanish health authorities have recently put into practice a strategy targeted at the prevention of obesity and overweight [12].

There is a clear genetic genetic component that predisposes a person to overweight-obesity [13] and other health disorders [14]. Thus, knowing the family history of body weight status and immune system related disorders (infections and allergies) is extremely useful. In addition, the home environment will often determine the healthy or non-health lifestyle of an adolescent. Hence, information regarding lifestyle in the family environment of adolescents can improve our understanding of their health status and predisposition to disease [15].

Physical inactivity seems to be a prominent risk factor for developing overweight and obesity. Despite cross-sectional studies having only found moderate relationships between levels of physical activity and weight status, prospective studies have linked low levels of physical activity with high weight gain over time [16]. In addition, experimental studies have shown that physical exercise increases the efficacy of weight loss programmes and seems to be a critical factor for weight maintenance over time [17]. Secular trends over the last forty years have also revealed that increased patterns of overweight and obesity show a stronger association with intensely sedentary behaviour than with a high calorie intake [18,19]. Exercise programmes have been demonstrated to reduce the body fat percentage in overweight children and adolescents [3] and there is also evidence indicating that active children have lower body fat proportions than their inactive peers.

Physical activity can be linked to most biological cardiovascular risk factors and metabolic disorders [20]. Thus, physical activity has been shown to reduce blood pressure in adults with high blood pressure, and also to reduce blood triglyceride levels and increase HDL-c concentrations. Studies have also shown that physical activity may improve insulin resistance and glucose tolerance, along with coagulation characteristics linked to thromboembolic phenomena. Similar beneficial effects to those found in adults have been described in children and adolescents related to glucose regulation, insulin sensitivity, as well as high blood pressure, HLD-c and triglyceride levels [3].

Current research efforts are being made to address the existing relationship between obesity and immunocompetence [21] and its impact on the long-term development of metabolic disorders and cardiovascular diseases. Obese subjects suffer from sub-clinical inflammation, which has been suggested to induce insulin resistance and metabolic syndrome [22]. Obesity could also affect the defence capacity of the immune system making obese subjects more susceptible to infection [23] or allergies [24].

### Study aims

The main aim of the AFINOS Study (La Actividad Física como Agente Preventivo del Desarrollo de Sobrepeso, Obesidad, Alergias, Infecciones y Factores de Riesgo Cardiovascular en Adolescentes; Physical Activity as a Preventive Measure for Overweight, Obesity, Infection, Allergies and Cardiovascular Risk Factors in Adolescents) is to examine relationships between regular physical activity levels in adolescents and overweight, infection and allergies, along with metabolic and immune system markers used to evaluate their health status. Our working hypothesis is that adolescents who more often undertake physical activity (excluding intensive training targeted at sports performance) are healthier and enjoy a better quality of life. In addition, this study seeks to establish the general prevalence of overweight-obesity and immune system-related disorders (infections and allergies) in the study population (adolescents aged 13 to 16 living in the Madrid region). Also examined was the potential influence of the family environment and lifestyle in developing a disease or acquiring (un)healthy habits that could eventually lead to an obesity-related disorder.

The study includes three surveys conducted on three different study populations: (a) Study 1 performed on a sample of 2400 adolescents; (b) Study 2 on a sample comprised of the parents of these adolescents; and (c) Study 3 performed on 200 of the adolescents included in (a) to assess in detail their physical activity levels and health status. The aims of each of these sub-studies are outlined below:

(a) Aims of Study 1 conducted on a representative sample of adolescents living in the Madrid region

1. To determine the prevalences of overweight, obesity, infections and allergies.

2. To assess physical activity and sedentary habits.

3. To assess basic eating habits.

4. To assess the relationship between sedentary lifestyle and the prevalence of health disorders (obesity, infections and allergies).

5. To asses the relationship between sedentary lifestyle and academic performance.

(b) Aims of Study 2 conducted on the adolescents' parents

1. To assess physical activity and sedentary habits.

2. To assess basic eating habits.

3. To assess the relationship between sedentary lifestyle and the incidence of certain chronic diseases (obesity, infections, allergies, cardiovascular risk factors and metabolic or cardiovascular diseases).

(c) Combined aims of Studies 1 and 2

1. To assess the relationship between obesity and susceptibility to infection in the adolescents and their parents.

2. To assess the relationship between physical activity and physical inactivity patterns in the adolescents and their parents.

3. To assess the relationship between the basic eating habits of the parents and basic eating habits of the adolescents involved in the study.

(d) Aims of Study 3 conducted on a subset of 200 adolescents

1. To assess the relationship between physical activity habits, physical fitness level and biochemical and immunological markers.

2. To assess the relationship between body composition (underweight/overweight/obesity) and biochemical and immunological profiles.

3. To assess the relationship between basic eating habits and biochemical and immunological profiles.

4. To assess the relationship between biochemical/immunological profiles and allergies, infections and cardiovascular risk factors.

## Methods/Design

The AFINOS Study is a multidisciplinary, cross-sectional, multicenter study endorsed by the National Research & Development & Innovation Plan of the Spanish Ministry of Education and Science, under the Strategic Line of Sport and Physical Activity. The three research groups involved are each specialized in a specific area of knowledge: (a) the Immunonutrition Research Group, Department of Metabolism and Nutrition, Scientific National Research Council (CSIC); (b) the Epidemiology Group, Department of Preventive Medicine and Public Health, Universidad Complutense de Madrid; and (c) the Physical Activity and Health Group. Department of Physical Education, Sport and Human Motricity, Universidad Autónoma de Madrid.

### Research universe and study samples

The AFINOS Study takes as universe, the population of adolescents aged 13 to 16 of the Madrid region (central Spain) and their parents. The Madrid Region is one of the country's most densely populated areas. With an extension of 8028 km^2 ^representing a mere 1.5% of the geographic area of Spain, the Madrid province is home to 13.5% of the entire Spanish population. According to the 2006 census of the National Statistics Institute http://www.ine.es, in this year there were 228,535 adolescents aged 13 to 16 living in the Madrid region, representing 12.7% of the Spanish adolescent population of this age group. Of these adolescents, 104,725 lived in Madrid City, 100,610 in its suburbs and 23,200 in the villages of the region.

The sample size for Study 1 was calculated using the Schlesselmann formula [25] for known population sizes, taking 0.05 as the maximum permissible error (reliability of 95%). In the calculation, we used the estimated variance for obese plus overweight subjects in our population of 20% indicated by data from the AVENA national study [10].

The final sample size calculated at 1998 individuals was increased by 20% to compensate for possible dropouts or data losses to give a final sample size of 2400 adolescents of both sexes.

According to the geographic distributions of adolescents in the Madrid region: 46% of the sample (1058 subjects) was selected from Madrid City, 35% (805 subjects) from its suburbs and 19% (435 subjects) from its villages. A randomised cluster sample procedure was used to select the sample. The first level of sampling was the entire set of secondary schools of the Madrid region. Thus, of 25 schools selected, 10 schools were in the city, 8 in the suburbs, and 7 schools in villages. The second level of sampling was school classroom/grade (2nd, 3rd and 4th years of Compulsory Secondary Education and first year of Non-Compulsory Secondary Education, according to the Spanish education system). The sample for Study 2 was comprised of the parents of the adolescents selected for Study 1.

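### The Study 1 sample size of 1998 does not follow from its stated inputs, which give about 246, and no design effect is reported for the 25-school cluster sample

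*Protocol article*

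**What the plan says.** All the material is in the protocol article, Methods/Design, Research universe and study samples.

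- Method: "The sample size for Study 1 was calculated using the Schlesselmann formula [25] for known population sizes".
- Error and confidence: "taking 0.05 as the maximum permissible error (reliability of 95" per cent).
- Prevalence input, credited to an earlier national study of adolescents: "we used the estimated variance for obese plus overweight subjects in our population of 20" per cent.
- Population: "in this year there were 228,535 adolescents aged 13 to 16 living in the Madrid region".
- Result: "The final sample size calculated at 1998 individuals was increased by 20% to compensate for possible dropouts or data losses", which brings the target to 2400.
- Design: "A randomised cluster sample procedure was used to select the sample", with classroom or grade as the second stage. On the number of clusters: "of 25 schools selected, 10 schools were in the city, 8 in the suburbs, and 7 schools in villages".

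No design effect, intraclass correlation or subgroup multiplier is given. The area counts in the same section (1058, 805 and 435) add to 2298.

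**The concern.** The paragraph supplies everything a single-proportion precision calculation needs: population, error, confidence, prevalence and result. A reader can therefore repeat it, and the result does not come out. A margin of 5 points around a prevalence near 20% needs a few hundred respondents under simple random sampling, not two thousand.

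This matters because the first listed aim of Study 1 is to estimate prevalences in a representative sample, so precision is its main design quantity. As written, a reader cannot tell what precision was intended, whether it applies overall or within subgroups, or whether the clustering described in the same paragraph was allowed for. The mismatch is not a product of condensing a longer document, because the inputs and the result are both printed and they disagree.

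**Working it through.** **Inputs from the article:** N = 228,535; e = 0.05; 95% confidence (z = 1.96); p = 0.20; stated result 1998; 25 schools.

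**Formula.** The cited source of the formula is not at hand, so I use the standard precision formula for one proportion with finite-population correction: n0 = z²·p(1−p)/e², then n = n0 / (1 + (n0 − 1)/N).

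**Attempt to reproduce 1998**

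- As stated: n0 = 3.8416 × 0.16 / 0.0025 = 245.9; n = 245.6, so 246.
- 20% taken as the variance: n0 = 3.8416 × 0.20 / 0.0025 = 307.3; n = 306.9, so 307.
- Worst case p = 0.5: n0 = 3.8416 × 0.25 / 0.0025 = 384.2; n = 383.5, so 384.
- 99% confidence, p = 0.20: 424.
- 0.05 as a relative error (±1 point): 5986. A 10% relative error (±2 points): 1527.
- Formula applied separately in city, suburbs and villages: 246 + 246 + 244 = 736.

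None gives 1998. The ratio to the as-stated result is 1998 / 246 = 8.12.

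**What would give about 1998**

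- A smaller error: e = 1.96 × √(0.16 / 1998) = 0.0175, i.e. ±1.75 points under simple random sampling. This contradicts the stated 0.05.
- Eight subgroups of 246 each: 8 × 246 = 1968. Four ages by two sexes would make eight, but the article does not say so.
- A design effect of 8.12. With 1998 / 25 = 79.9 pupils per school, the ICC would be (8.12 − 1) / (79.9 − 1) = 0.090. With 2400 / 25 = 96 per school it would be 7.12 / 95 = 0.075. The article gives no ICC.

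**Loss allowance.** 1998 × 1.2 = 2397.6, rounded to 2400. This step reproduces.

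**Precision with clustering.** As a cautious base I take the 2298 from the area counts and lose 20%: 2298 × 0.8 = 1838, or 73.5 per school. The half-width under simple random sampling at p = 0.20 is 1.96 × √(0.16 / 1838) = 1.83 points. The design effect is 1 + (73.5 − 1) × ICC, and the half-width is multiplied by its square root. The ICC values are my assumptions.

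| ICC (assumed) | Design effect | Half-width (points) |
|---|---|---|
| 0.01 | 1.73 | ±2.4 |
| 0.02 | 2.45 | ±2.9 |
| 0.05 | 4.63 | ±3.9 |
| 0.09 | 7.53 | ±5.0 |

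**The case against.** **The 0.05 may be the alpha level.** It stands next to the 95% figure. On that reading no margin of error is stated, and 1998 is under-described rather than contradicted. This is strained: a maximum permissible error is ordinarily a margin, and the next paragraph, on Study 3, uses the term alpha error when it means alpha. Even if accepted, it leaves 1998 without a stated basis.

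**An allowance may have been made but not printed.** A design effect near 8, or eight age-by-sex cells, would come close to 1998. This stands as a limit on the diagnosis. Failure to reproduce shows that the reported inputs are wrong or incomplete, but not which one. A reader might infer that the investigators ignored clustering; the article supports only the narrower statement that no design effect is reported.

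**±1.75 points is not a target of the study.** This also stands. A reader might infer that the cluster sample misses its intended precision because ±2.4 to ±3.9 is wider than ±1.75. But ±1.75 is obtained only by working back from 1998. The one stated error is 0.05, and the recomputed range lies inside it.

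**The 20% increase is not an error.** A reader might object that 1998 / 0.8 = 2498 would be needed to keep 1998 after a 20% loss. The article says only that the number was raised by 20%, which is what was done. It does not say that 20% of those enrolled are expected to be lost.

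**Conclusion.** The point holds as a defect in the stated justification. The printed inputs give about 246 (307 or 384 on the nearest alternative readings), so 1998 is about eight times what they support. The paragraph also describes a two-stage cluster sample without reporting any term for it.

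The conclusion rests on the standard one-proportion formula and on reading 0.05 as an absolute margin. A relative margin does not give 1998 either.

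It does not extend to the study being too small. At about 1838 analysed, the half-width at 20% prevalence passes ±5 points only when the ICC is near 0.09 or more; at an ICC of 0.01 to 0.05 it is about ±2.4 to ±3.9. The 1838 assumes both the 2298 total and a full 20% loss. The gap between 2298 and 2400 is a separate matter and is used here only to keep the precision figures cautious.

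**What to change.** Rewrite the Study 1 sample-size paragraph so that it reproduces 1998 from the inputs actually used:

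- the margin of error, and whether it is absolute or relative;
- the prevalence, worded as a prevalence if that is what the 20% is;
- any design effect or subgroup multiplier, with the subgroups named.

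If ±5 points was meant within subgroups, say so. Replace the bare ±5 basis with the cluster-adjusted half-width expected from 25 schools under a stated ICC, preferably over a short range of values. If the inputs can no longer be recovered, say that and let the cluster-adjusted precision stand as the justification.

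The cost is one rewritten paragraph and a short calculation, with no extra participants and no change to data collection.

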#### Statistical analysis

The final data will be analyzed using SPSS and SAS software. Frequencies and distributions of the variables will be determined using descriptive statistics that will serve to determine the general situation of the study subjects. Quantitative variables will be expressed as means and standard deviations of the mean, except for age, which will be expressed as year-by-year frequencies (13-14-15 and 16), and qualitative variables will be expressed as absolute frequencies of every category and percentages related to the total number of valid cases. The normal distribution of quantitative variables will be checked through adequate tests. To determine possible associations, the Chi-squared test will be used for qualitative observations and the student *t-*test to compare independent means of the quantitative data [26]. Pearson's correlation coefficient will be used to analyse two quantitative variables and if these are not verified as normally distributed the Spearman correlation will be used [53]. When analysis of several variables is needed, a multivariate analysis using the forward stepwise multiple regression method will be performed to construct models to explain the variability observed in the population and assess the combined effect of different variables. Risk profiles will be generated by multiple logistic regression, determining adjusted regression coefficients to calculate the odds ratio for each variable.

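### The Study 1 allocation is said to follow the geographic distribution of adolescents, but its 46/35/19% split contradicts the census counts beside it (45.8/44.0/10.2%), and its stratum counts total 2298 against a stated 2400

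*Protocol article*

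**What the plan says.** All the figures stand in one section of the protocol article, Research universe and study samples.

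- **Population.** The census total is given as "there were 228,535 adolescents aged 13 to 16 living in the Madrid region", and its breakdown as "104,725 lived in Madrid City, 100,610 in its suburbs and 23,200 in the villages of the region".
- **Target size.** A calculated requirement of 1998 is raised by 20% "to give a final sample size of 2400 adolescents of both sexes".
- **Allocation.** The sentence on the split opens with "According to the geographic distributions of adolescents in the Madrid region" and continues: "46% of the sample (1058 subjects) was selected from Madrid City, 35% (805 subjects) from its suburbs and 19% (435 subjects) from its villages".
- **Schools.** The first sampling stage is described as "of 25 schools selected, 10 schools were in the city, 8 in the suburbs, and 7 schools in villages".

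The Study aims section calls the Study 1 sample representative of the Madrid region, and its first listed aim for Study 1 is the prevalence of overweight, obesity, infections and allergies. The Statistical analysis section says that qualitative variables will be reported as absolute frequencies and "percentages related to the total number of valid cases". The article does not mention stratum weights.

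**The concern.** The allocation sentence gives the geographic distribution of adolescents as its basis, but the split that follows is not the distribution printed just before it. The suburbs and villages are each about 9 percentage points away from their census share, in opposite directions. The stratum counts also do not add to the sample size that the section has just derived.

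Regional prevalence is the first aim of Study 1. An analyst who takes the allocation sentence at its word would treat the sample as self-weighting across strata and see no need for an adjustment. If the printed split is what was actually drawn, a pooled percentage estimates the prevalence of a population with nearly twice the real share of village adolescents and four-fifths of the real share of suburban ones. More respondents at the same split would not reduce that error.

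**Working it through.** **Inputs** (all from Research universe and study samples): population 104,725 / 100,610 / 23,200, total 228,535; sample 1058 / 805 / 435, stated as 46 / 35 / 19%; requirement 1998, inflation 20%, final size 2400; schools 10 / 8 / 7.

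**1. Is the census breakdown coherent?** 104,725 + 100,610 + 23,200 = 228,535, exactly the stated total. The contradiction therefore does not come from a misprinted census count.

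**2. Shares.** Population share W = stratum count / 228,535. Sample share f = stratum count / 2298.

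| | Census share W | Sample share f | f / W | f − W |
|---|---|---|---|---|
| City | 45.82% | 46.04% | 1.005 | +0.2 points |
| Suburbs | 44.02% | 35.03% | 0.796 | −9.0 points |
| Villages | 10.15% | 18.93% | 1.865 | +8.8 points |

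Rounding cannot produce gaps of 9 points. Proportional allocation would give about 1053 / 1012 / 233 of 2298, or 1100 / 1057 / 244 of 2400 (each rounded separately).

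**3. The schools.** 10 / 8 / 7 of 25 is 40 / 32 / 28%. In proportion to adolescents it would be about 11.5 / 11.0 / 2.5. School numbers need not be proportional if the numbers sampled per school differ, but they lean the same way, so a misprint confined to the percentages is less likely.

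**4. The total.** The plan's own figure first: 1998 × 1.20 = 2397.6, which reproduces 2400. The strata give 1058 + 805 + 435 = 2298, which is 102 (4.25%) fewer. Applying 46 / 35 / 19% to 2400 gives 1104 / 840 / 456, which are not the printed counts. Applied to 2300 it gives 1058 / 805 / 437, which matches two strata exactly and the third within 2. Also, 1998 × 1.15 = 2297.7, so the counts would fit a 15% inflation. That is a numerical coincidence worth asking about, not evidence of what was done.

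**5. Effect on an unweighted regional prevalence, if the split is real.**

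Bias = Σ(f − W)·p = +0.002·p(city) − 0.090·p(suburbs) + 0.088·p(villages).

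The article gives no prevalence by stratum, so the differences below are assumptions, with city and suburbs taken as equal:

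| Assumed village excess | Bias of the pooled percentage |
|---|---|
| 0 points | 0 |
| 2 points | +0.18 points |
| 5 points | +0.44 points |
| 10 points | +0.88 points |
| 15 points | +1.32 points |

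For scale, at the 20% overweight-plus-obesity figure used in the sample size calculation, the simple-random-sampling standard error with 2298 adolescents is √(0.20 × 0.80 / 2298) = 0.0083, or 0.83 points. Sampling was by school and classroom, so with positive correlation within schools the true standard error is larger and the relative weight of the bias smaller.

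**6. Weights and their cost, if the printed counts are the realised ones.** W / f = 0.995 city, 1.257 suburbs, 0.536 villages. Variance factor from weighting: Σ(W² / f) = 0.456 + 0.553 + 0.054 = 1.064 (terms rounded). The effective sample size is about 2298 / 1.064 = 2160.

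**The case against.** The arithmetic is hard to dispute, and nothing elsewhere in the article reconciles the figures. The case against concerns what may be built on it, and much of that case stands.

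- **A reader might infer that the trial has decided not to weight and that its regional prevalences are therefore biased toward the villages.** The article does not support this. It condenses a fuller plan that is not shown and could contain weights. The sentence on percentages of valid cases says how descriptive results are expressed; it neither sets nor rules out weights for regional estimates. Bias also arises only where prevalence differs by stratum, and no stratum prevalences are given.
- **A reader might infer that 2400 is simply wrong by 102, or that recruitment fell short.** Neither is shown. The 2400 follows from its own stated inputs, nothing labels 2298 as an achieved count, and 2298 still exceeds the requirement of 1998. What can be said is that the two figures conflict.
- **Fixed weights should not be taken from disputed counts.** If the real sample were proportional and the split a misprint, applying 0.995 / 1.257 / 0.536 would itself create a distortion: villages would count for 0.054 / 1.064 = 5.1% instead of 10.2%. In addition, the census counts go by where adolescents live while the sampling units are schools, and the article does not say whether the stratum definitions coincide.
- **The size is modest**, under one point even for an assumed 10-point difference. The Study aims put associations first and regional prevalence as an addition, and no effect on the associations has been shown.

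These points limit the consequence. They do not remove either contradiction: an allocation described as geographic that does not follow the geography given, and counts that do not add to the stated size.

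**Conclusion.** The point holds as an internal contradiction with a conditional consequence. Two things are established from the article's own figures, without assumptions: the 46/35/19% split does not follow the census distribution of 45.8/44.0/10.2%, and the stratum counts total 2298 where 2400 is stated. The first undercuts the claim that the sample represents the region, on which the first aim of Study 1 relies.

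The effect on results rests on three assumptions: that the printed split is the real one, that pooled percentages are reported for the region without adjustment, and that prevalence differs by stratum. Under these, the error is about 0.9 points for a 10-point village-suburb difference and 0.4 for 5 points. If the strata do not differ, it is zero.

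**What to change.** 1. Reconcile the allocation percentages, the stratum counts and the total. State whether 2400 or 2298 is the intended size, and whether the stratum counts are planned or achieved.
2. If the allocation was disproportionate, say so and remove the statement that it follows the geographic distribution. If it was proportional, correct the percentages and counts.
3. In the disproportionate case, estimate regional prevalences with stratum weights equal to census share over realised sample share, after confirming that the strata used for schools match those used for the census. If the printed counts prove to be the realised ones, the weights are about 0.995 / 1.257 / 0.536; otherwise recompute them. If the full analysis plan already specifies weights, a sentence in the article pointing to them is enough.

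The cost is a wording correction and one weight variable, both possible after data collection. Weighting raises variance by about 6% (factor 1.064 on the printed counts). That figure covers weighting only and not the clustering by school.
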